### Secondary Outcome Measures

#### Overview

The secondary outcome measures are psychiatric comorbidity, everyday functioning, emotional deregulation, problematic social media behavior, gaming motives, symptoms of problem gambling, alcohol use, substance use, harm severity of gaming, therapeutic alliance, and treatment satisfaction.

#### Adults

Psychiatric comorbidity is measured by semistructured interviews by a clinician with the Mini International Neuropsychiatric Interview which assesses common psychiatric diagnoses from the *DSM-V* and *International Classification of Diseases, 10th Revision* (*ICD-10*) [51]. Everyday functioning is measured by clinicians using the Global Assessment of Functioning [52], where the clinician assesses everyday function on a 1-100 scale. Emotional dysregulation is measured using the Difficulties in Emotion Regulation Scale-16 [53], which consists of 16 items. Problematic social media use is measured with the Bergen Social Media Addiction Scale, which contains 6 questions answered on a 5-point Likert scale, from 1 to 5, about salience, mood modification, tolerance, withdrawal, conflict, and relapse [54]. Gaming motives are assessed using the Motives for Online Gaming Questionnaire, which contains 27 questions answered on a 5-point Likert scale, from 1 to 5 [55]. The questionnaire assesses 7 motivational factors: escape, coping, competition, social, skill development, fantasy, and recreation. Problem gambling is measured with the National Opinion Research Centre Diagnostic Screen for Gambling Disorders–Preoccupation, Escape, Risked Relationships, and Chasing, consisting of 4 questions about gambling problems throughout one’s lifetime, focusing on preoccupation, chasing losses, escape, and the social consequences of gambling, answered on a binary scale. If the participant endorses any item, it indicates problem gambling [56]. To assess the level of alcohol consumption, we use the Alcohol Use Disorders Identification Test-Consumption scale, 3 questions, which focus on the frequency and quantity of alcohol consumption [57]. To measure substance use behavior, a drug identification list consisting of 10 common substances is given to the patients from which they indicate whether they have ever used said substance, and if so, how often. Gaming-related harm severity was assessed by questions about how the patient’s gaming impairs their ability to function in school or work, everyday situations at home, social activities, free time, and family life. The scale ranges from 0 (indicating no harm or minimal impact) to 10 (signifying severe harm) on how gaming impairs their function in the 5 parts of their everyday life. The therapeutic alliance is measured by the Working Alliance Inventory Short, which contains 12 questions about the alliance in the therapeutic relationship [58]. Further, 9 additional questions were developed by the research team and included regarding patient treatment satisfaction.

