### Outcome Measures

This study consists of children, adolescents, and adults, as well as their parents. The patients will have different outcome measures depending on whether they are children (aged 13-15 years) or adults (aged 16 years and older). When the patient is a child, some outcome measures will also be collected from parents. An overview of outcome measures and assessment points is shown in Tables 1 and 2.

**Table 1 table1:** Measures’ and measurements’ points for adults, aged 16+ years.

Measure	Outcome	Assessment	Treatment period			
		Baseline	Pretreatment	Weekly	Posttreatment	Month 3
CORE-OM 34^a^	Primary	✓	✓		✓	✓
GDT^b^	Primary	✓			✓	✓
IGDS9-SF^c^	Primary	✓			✓	✓
Time spent gaming	Primary	✓	✓	✓	✓	✓
How do you feel?	—^d^			✓		✓
Demographic	—	✓				
MINI^e^ interview	Secondary	✓			✓	
GAF^f^	Secondary	✓			✓	
NODS-PERC^g^	Secondary	✓			✓	
Social media disorder	Secondary	✓			✓	
Game motives	Secondary	✓			✓	
Emotion regulation	Secondary	✓			✓	
Alcohol use	Secondary	✓			✓	
Substance use	Secondary	✓			✓	
Harm severity of gaming	Secondary	✓			✓	
Working alliance	Acceptability					
Treatment satisfaction	Acceptability					

^a^CORE-OM 34: Clinical Outcomes in Routine Evaluation–Outcome Measure 34 questions.

^b^GDT: Gaming Disorder Test.

^c^IGDS9-SF: Internet Gaming Disorder Scale–Short-Form.

^d^Not applicable.

^e^MINI: Mini International Neuropsychiatric Interview.

^f^GAF: Global Assessment of Functioning.

^g^NODS-PERC: National Opinion Research Centre Diagnostic Screen for Gambling Disorders–Preoccupation, Escape, Risked Relationships, and Chasing.

**Table 2 table2:** Measures’ and measurements’ points for children, aged 13-15 years.

Measure	Outcome	Assessment	Treatment period			
		Baseline	Pretreatment	Weekly	Posttreatment	Month 3
RCADS^a^-child	Primary	✓	✓		✓	✓
RCADS-parent	Primary	✓	✓		✓	✓
GDT^b^	Primary	✓			✓	✓
IGDS9-SF^c^	Primary	✓			✓	✓
GAIT^d^-parent	Primary	✓			✓	✓
Time spent gaming	Primary	✓	✓	✓	✓	✓
How do you feel?	—^e^			✓		
Demographic	—	✓				
MINI^f^-kid interview	Secondary	✓			✓	
CGAS^g^	Secondary	✓			✓	
NODS-PERC^h^	Secondary	✓			✓	
Social media disorder	Secondary	✓			✓	
Game motives	Secondary	✓			✓	
Emotion regulation	Secondary	✓			✓	
Alcohol use	Secondary	✓			✓	
Substance use	Secondary	✓			✓	
Harm severity of gaming	Secondary	✓			✓	
Working alliance	Acceptability				✓	
Treatment satisfaction	Acceptability				✓	

^a^RCADS: Revised Child Anxiety and Depression Scale.

^b^GDT: Gaming Disorder Test.

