
#### Children

In total, 2 of the instruments are different between the children and adults. Psychiatric comorbidity is measured by using the Mini International Neuropsychiatric Interview for Children and Adolescents [59]. Everyday functioning is measured by the clinician using the Children’s Global Assessment Scale [60], where clinicians assess everyday function on a scale from 1 to 100.

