### Statistical Analysis and Power Analysis

We will present descriptive statistics (eg, proportions, means, SD, and medians) and bivariate correlation measures for variables collected at baseline. To assess the overall effect of the treatment phase (baseline, postintervention, and follow-up) on primary (eg, GD symptom burden, psychological distress, and time spent gaming) and secondary continuous outcome measures, we will conduct repeated measures mixed-effect ANOVA with time as a fixed factor and patient as a random factor; post hoc pairwise comparisons with Bonferroni corrections will be conducted to determine differences in outcome variables across treatment phases. This approach is essentially equivalent to repeated measures ANOVA but will enable us to control individual variability and perform analyses including all cases provided each patient has 1 valid pre- or postoutcome value. In addition, we will conduct logistic mixed-effect model analyses to assess the effect of time on binary outcome measures (ie, symptom improvement).

All tests will be 2-sided with the α level set at .05. Based on previous CBT-based therapy studies for GD that indicate medium-to-large effect sizes from pre- to posttest for symptom burden, time playing, and mental health improvement [32], we estimate that a minimum of 28 participants would be required to achieve 80% power to detect such differences across all outcome measures (Cohen *f*=0.25). To accommodate a potential attrition rate of 30%, we will enroll a minimum of 37 participants for quantitative analyses. Follow-up univariate logistic regressions will be conducted to explore which baseline characteristics are predictive of participant symptom improvement, defined by subcutoff scores for the GDT, IGDS9-SF, and CORE-OM 34 follow-up. Planned analyses will be conducted apropos of missing data patterns and modified accordingly when needed. The results will be reported as means and odds ratios, respectively, with 95% CIs.

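### Problem gambling is a pre-post secondary outcome but is screened over the lifetime, so its status cannot show improvement; the same holds for the ever-used part of the substance list

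*Protocol article*

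**What the plan says.** Under Secondary Outcome Measures, the Overview of the protocol article lists among the secondary outcomes "gaming motives, symptoms of problem gambling, alcohol use, substance use, harm severity of gaming". Tables 1 and 2 (Outcome Measures) mark NODS-PERC and substance use as secondary, each assessed at baseline and at posttreatment.

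The Adults subsection describes the gambling screen as "consisting of 4 questions about gambling problems throughout one’s lifetime", on a binary response scale, with this rule: "If the participant endorses any item, it indicates problem gambling". For substance use, patients get a list of 10 substances, on which "they indicate whether they have ever used said substance, and if so, how often".

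The Children subsection states: "In total, 2 of the instruments are different between the children and adults". The two are the diagnostic interview and the functioning scale, so the same gambling and substance questions apply at ages 13 to 15.

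Statistical Analysis and Power Analysis plans mixed-effect ANOVA over time for the primary and the continuous secondary outcomes. For binary outcomes it says: "we will conduct logistic mixed-effect model analyses to assess the effect of time on binary outcome measures (ie, symptom improvement".

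**The concern.** A pre-post outcome has to be able to move in both directions. A lifetime question cannot, because a past event is not undone by treatment. If gambling status is compared between baseline and posttreatment as described, no change would say nothing about benefit, and a fall would point to recall or response error rather than recovery. A patient who already screens positive at baseline also keeps the same status if gambling gets worse, although further items may be endorsed.

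The study has one arm and no control group, so within-patient change is its only internal evidence of effect. A measure whose change can go in only one direction adds nothing on improvement.

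**Working it through.** The article gives no figure on this point to reproduce. The check is a matter of logic, with a small illustration.

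**Inputs from the article**
- Gambling screen: 4 binary items, lifetime recall, any positive item classifies (Secondary Outcome Measures, Adults).
- Substance list: 10 substances, ever used, plus how often, with no recall window for the frequency part (same subsection).
- Timing: baseline and posttreatment (Tables 1 and 2).
- Illustration size: 37 patients, the minimum enrolment in Statistical Analysis and Power Analysis. The conclusion does not depend on it.

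**Logic for one lifetime item**
- Truthful answers satisfy: post = baseline OR new onset.
- So P(yes at baseline, no at posttreatment) = 0.
- If each of the 4 items can only stay or rise, so can the any-item status and the count of positive items.
- The same holds for ever-use of each of the 10 substances.

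**Expected change in the proportion positive**

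Let p be baseline prevalence, i new onset during treatment and r remission among baseline positives. The article gives none of these. The assumed ranges are p = 5% to 30%, i = 2% and r = 0%, 50% or 100%. All baseline positives are taken to be current cases, so that the two kinds of wording can be compared.
- Lifetime wording: change = i(1 − p). Remission does not appear in it.
  - p = 0.05: 0.02 × 0.95 = +0.019
  - p = 0.30: 0.02 × 0.70 = +0.014
- Current-state wording: change = p(1 − r) + i[1 − p(1 − r)] − p.
  - p = 0.05, r = 0.5: 0.025 + 0.02 × 0.975 − 0.05 = −0.0055
  - p = 0.30, r = 1: 0 + 0.02 − 0.30 = −0.28

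**Simulation of the same scenarios (37 patients, 20,000 simulated studies each)**

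| Baseline prevalence | Remission | Lifetime change | Current-state change |
|---|---|---|---|
| 5% | 0% | +0.0191 | +0.0191 |
| 5% | 50% | +0.0188 | −0.0056 |
| 5% | 100% | +0.0192 | −0.0296 |
| 30% | 0% | +0.0139 | +0.0139 |
| 30% | 50% | +0.0137 | −0.1327 |
| 30% | 100% | +0.0138 | −0.2805 |

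Across all scenarios, including prevalences of 10% and 20%, the smallest lifetime change in any simulated study was 0. The mean lifetime change was +1.4 to +1.9 percentage points, all of it assumed new onset, and essentially the same at 0%, 50% and 100% remission. With 50% to 100% remission, the current-state item fell by 0.6 to 28 points.

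**Substance frequency**

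This part differs. If how often refers to a recent period, it can fall. If it refers to the lifetime, it is as insensitive as ever-use. The article does not say which. By contrast, it ties time spent gaming to the last week.

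**The case against.** **Substance use.** A reader might infer that substance use as a whole cannot improve. The document does not support that: the question goes on to ask how often, and a frequency with a recent reference period can fall. A condensed article may leave that period to the full protocol, so its absence is not itself an error. This part of the objection stands, and the point is limited to ever-use.

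**What stays visible.** A reader might also infer that only new onset in baseline-negative patients can be seen. That goes too far. A patient positive on one gambling item can later endorse others, and a baseline user can report a new substance or, depending on the recall period, more frequent use. Some worsening therefore remains visible among baseline positives. Improvement in gambling status or ever-use does not.

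**Purpose.** Nothing in the article says these measures are meant to detect a shift from gaming into gambling or drugs. The effectiveness objective under Aims and Objectives covers gaming disorder symptoms, distress and gaming time.

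**Planned test.** No sentence commits to a test of gambling status over time. The logistic model is tied to symptom improvement, which is defined only through cutoffs on the GDT, IGDS9-SF and CORE-OM 34. This is fair. Still, a measure declared a secondary outcome and scheduled before and after treatment invites that comparison, and no analysis plan could recover remission from a lifetime yes or no.

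**Weight.** Gambling and substance use are two of eleven secondary domains in a study that calls itself exploratory, and the share of patients positive at baseline is unknown. This limits the importance of the point, not its correctness.

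**Conclusion.** The point holds for NODS-PERC in full. As described, problem-gambling status cannot truthfully move from positive to negative, so the largest true reduction is 0 at any remission rate. The article describes no current-period version of the screen. It holds equally for ever-use of each listed substance. For substance-use frequency, sensitivity to change cannot be judged from the article.

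This rests on two assumptions: that patients answer truthfully, and that the posttreatment questionnaire keeps the lifetime wording given in the article. The prevalence, onset and remission values in the illustration are assumed and do not affect the direction of the result.

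The consequence is limited. The primary outcomes and the sample size are untouched; only the reading of these secondary outcomes is affected.

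**What to change.** - **Remaining patients:** ask the NODS-PERC items over the same recent window at baseline and at posttreatment, and state that window.
- **Patients already assessed with lifetime wording:** report lifetime gambling status and ever-use as baseline descriptors, plus new onset (gambling items or substances newly endorsed at posttreatment). Do not analyse them as pre-post improvement outcomes.
- **Substance-use frequency:** state its reference period. If it is recent, keep frequency as the pre-post substance measure.

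The cost is a change of recall wording on a four-item screen and a sentence or two in the plan; the reclassification needs no new data. The drawback is that patients already assessed lack the recent-window gambling items. Recruitment runs from March 2022 to August 2024, so a change of wording partway leaves two versions in the data, and the two should be reported separately. If few or no patients remain to be assessed, reclassification alone is enough.

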
#### Children

In total, 2 of the instruments are different between the children and adults. Psychiatric comorbidity is measured by using the Mini International Neuropsychiatric Interview for Children and Adolescents [59]. Everyday functioning is measured by the clinician using the Children’s Global Assessment Scale [60], where clinicians assess everyday function on a scale from 1 to 100.

### Additional Measures

Data concerning demographics, what games they are playing, everyday gaming behavior, social life, family life, psychical health, sleep and eating habits, as well as symptoms of ASD and ADHD, are gathered at baseline to provide a comprehensive picture of the treatment-seeking sample. For the adults, ASD symptoms will be measured with Ritvo Autism and Asperger Diagnostic Scale 14 [61]. Symptoms of ADHD will be measured by the Adult ADHD Self-Report Scale part A, which contains 6 items, and it has been found that these questions are the most predictive of ADHD [62]. For children, patient-reported symptoms of ASD and ADHD are measured with Ritvo Autism and Asperger Diagnostic Scale 14 and Adult ADHD Self-Report Scale, respectively. Likewise, parent-reported child ASD and ADHD symptoms are measured using the Autism Quotient [63] and Swanson, Nolan, and Pelham [64] scales, respectively. After each treatment session, the patients will answer 4 questions: rating their psychological well-being on a 1-10 scale, reporting how much time they have spent gaming the last week, rating how much their psychological distress depends on their gaming on a scale of 1-10, and the reporting of how helpful they found this treatment session on a 1-10 scale. After treatment, the patients will be asked whether they have received any parallel interventions during the treatment and whether they will seek further help for their problems. Before treatment begins, the patients’ current medications will be documented. During the posttreatment assessment, any changes to their medications during the treatment will be recorded. These changes will be reported at the group level in the final paper.

### Sample Size

This study is performed in routine care and a naturalistic setting, which means that how many participants can be recruited is dependent on how many patients seek treatment at the said outpatient clinic. We aim to conduct semistructured interviews with at least 20 participants, both patients and parents, or until data saturation is reached.

### Statistical Analysis and Power Analysis

We will present descriptive statistics (eg, proportions, means, SD, and medians) and bivariate correlation measures for variables collected at baseline. To assess the overall effect of the treatment phase (baseline, postintervention, and follow-up) on primary (eg, GD symptom burden, psychological distress, and time spent gaming) and secondary continuous outcome measures, we will conduct repeated measures mixed-effect ANOVA with time as a fixed factor and patient as a random factor; post hoc pairwise comparisons with Bonferroni corrections will be conducted to determine differences in outcome variables across treatment phases. This approach is essentially equivalent to repeated measures ANOVA but will enable us to control individual variability and perform analyses including all cases provided each patient has 1 valid pre- or postoutcome value. In addition, we will conduct logistic mixed-effect model analyses to assess the effect of time on binary outcome measures (ie, symptom improvement).

All tests will be 2-sided with the α level set at .05. Based on previous CBT-based therapy studies for GD that indicate medium-to-large effect sizes from pre- to posttest for symptom burden, time playing, and mental health improvement [32], we estimate that a minimum of 28 participants would be required to achieve 80% power to detect such differences across all outcome measures (Cohen *f*=0.25). To accommodate a potential attrition rate of 30%, we will enroll a minimum of 37 participants for quantitative analyses. Follow-up univariate logistic regressions will be conducted to explore which baseline characteristics are predictive of participant symptom improvement, defined by subcutoff scores for the GDT, IGDS9-SF, and CORE-OM 34 follow-up. Planned analyses will be conducted apropos of missing data patterns and modified accordingly when needed. The results will be reported as means and odds ratios, respectively, with 95% CIs.

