## Methods

### Study Design and Setting

This study has a single group with a pretest, posttest, and 3-month follow-up design, as well as measures at each session. It is conducted in routine care and the participants are treatment-seeking patients. This study will be carried out at a single site, Gamingprojektet Maria Malmö, which is an outpatient clinic for problematic gaming behavior and GD in Skåne, Sweden. The participants will be offered a module-based psychotherapy that is a combination of interventions from CBT and FT. The treatment will be given by psychologists with a 5-year education in clinical psychology and psychotherapy, social workers with 1-year training in psychotherapeutic counseling, and psychotherapists with 2.5 years training in psychotherapeutic counseling. The treatment can be given as an individual treatment with the patient, a family treatment with only the parents, or a family treatment with both the parents and the patient. Most treatments will be conducted with 1 clinician per treatment, but exceptions can be made if there is a high level of conflict between the patient and the parents. Assessment points include baseline, which is the assessment period; the start of therapy (pretreatment period); the end of therapy (posttreatment period); and the follow-up after 3 months. In addition to these quantitative measures, we will also conduct qualitative interviews with patients and relatives about their views on the outcome, acceptability, and eventual negative experiences of the treatment, which will be presented in a separate paper.

A Transparent Reporting of Evaluations With Nonrandomized Designs 2004 flow diagram [44] of this study’s design is shown in Figure 1. This study is registered with ClinicalTrials.gov (NCT06018922). Recruitment started March 17, 2022, and will close on August 30, 2024.

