### Limitations and Strengths

The primary limitation of this study is its single-arm design, with 1 intervention group and no control group. This design makes it hard to draw any definitive conclusions about the effectiveness of the treatment, as opposed to potential influences from the patient–health care professional interactions or the natural course of the disorder’s reduction over time. However, we can compare our results with outcomes from other studies on treatment for GD. Several factors influenced our decision to pursue a single-group trial design. First, we anticipated recruitment challenges given that this study would be conducted at a newly established clinic. Ethical considerations also played a part; we felt it imperative to offer the best possible treatment to those seeking assistance, rather than withholding potential benefits for the sake of a control group. There is no established treatment for GD, and therefore, we could not have another treatment arm in this study. Due to recruitment challenges, in terms of few patients seeking treatment for GD and a lack of awareness about the newly opened clinic, we decided not to use a waiting list control group. Lastly, given this study’s exploratory nature, our objective was to evaluate the treatment in a real-world setting, examine how many sessions the clinicians often offer, and which of the modules are most often used.

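### The outcome model starts at the assessment-period baseline and gives no role to the scheduled start-of-therapy values, so the effect on distress and gaming time may include change before therapy

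*Protocol article*

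**What the plan says.** Study Design and Setting treats baseline and the start of therapy as two different occasions: "Assessment points include baseline, which is the assessment period; the start of therapy (pretreatment period); the end of therapy (posttreatment period"; the 3-month follow-up completes the list.

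Tables 1 and 2 (Outcome Measures) show which outcomes are measured on both occasions:

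- **Baseline and pretreatment:** CORE-OM 34 (age 16 and over), RCADS-child and RCADS-parent (age 13-15), and time spent gaming (both age groups). All are labelled primary.
- **Baseline but not pretreatment:** GDT, IGDS9-SF and GAIT-parent, also labelled primary, and all the secondary scales.

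Statistical Analysis and Power Analysis sets the time points of the model with the words "To assess the overall effect of the treatment phase (baseline, postintervention, and follow-up) on primary". It then specifies the method: "we will conduct repeated measures mixed-effect ANOVA with time as a fixed factor and patient as a random factor". Pairwise comparisons between phases are Bonferroni-corrected. The pretreatment occasion does not appear in this or any other stated analysis.

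Limitations and Strengths says "The primary limitation of this study is its single-arm design, with 1 intervention group and no control group". It adds "This design makes it hard to draw any definitive conclusions about the effectiveness of the treatment", and names patient-professional interactions and the natural course of the disorder as rival explanations.

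**The concern.** What the model calls the treatment phase begins at an occasion that the design section places in the assessment period. For distress and gaming time, any movement between assessment and the start of therapy is counted in full in the baseline-to-post difference, which is the quantity a reader will take as the treatment effect.

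With no control group, little inside the trial can separate treatment from natural course. For these outcomes the baseline-to-pretreatment pair is the only scheduled repeat measurement before therapy. It bears directly, though only in part, on a rival explanation that the protocol itself raises, and it has no stated role. Two of the three primary constructs (distress and gaming time) are affected in a way the analysis could address. For the third, GD symptoms, the same change may be included but cannot be separated with the scheduled data.

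**Working it through.** **1. Is the three-point reading the intended one?** The sample size helps to answer this.

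- From the protocol: f = 0.25, two-sided alpha 0.05, 80% power, N = 28.
- Assumed, because not stated: correlation rho between occasions, and sphericity.
- Formula for a within-subject test with m occasions: lambda = N·m·f²/(1 − rho), with degrees of freedom m − 1 and (N − 1)(m − 1).
- For m = 3, rho = 0.5, N = 28: lambda = 28 × 3 × 0.0625/0.5 = 10.5, degrees of freedom 2 and 54, power 0.81. N = 28 is the smallest N that reaches 80%.
- At the same rho, m = 2 needs 34 and m = 4 needs 24. With m = 3, rho = 0.3 needs 38 and rho = 0.7 needs 17.

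Among these variants only three occasions at rho = 0.5 gives the stated 28. This agrees with the time points listed in the text and with pretreatment being left out of the model.

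**2. What could the omission do?** Suppose the mean falls by d SD between baseline and pretreatment and does not change after therapy starts. The baseline-to-post difference is then d, all of it from before therapy.

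- n = 28 is the protocol's minimum. It can serve for gaming time only, because CORE-OM and RCADS are each collected in one age group and so have fewer patients.
- Three pairwise comparisons under Bonferroni: alpha = 0.05/3 = 0.0167. The critical t on 27 degrees of freedom is 2.55.
- Standardised paired difference: dz = d/√(2(1 − rho)). Noncentrality = dz·√28.
- Example, d = 0.2 and rho = 0.5: dz = 0.2/√1 = 0.2; noncentrality = 0.2 × 5.292 = 1.06; probability of significance 0.08.
- Example, d = 0.3 and rho = 0.7: dz = 0.3/√0.6 = 0.387; noncentrality = 2.05; probability 0.33.

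| Assumed drift before therapy | rho = 0.5 | rho = 0.7 |
|---|---|---|
| 0.1 SD | 3% | 4% |
| 0.2 SD | 8% | 14% |
| 0.3 SD | 19% | 33% |
| none (nominal) | 1.7% | 1.7% |

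In the same scenario a pretreatment-to-post contrast compares two equal means and keeps its nominal level.

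**3. Would a fourth level cost patients?** With m = 4, rho = 0.5 and f = 0.25, lambda at N = 28 is 28 × 4 × 0.0625/0.5 = 14 and the power of the overall test is 0.88. On these assumptions the overall test needs no extra patients. Four levels do give 4 × 3/2 = 6 pairwise comparisons instead of 3, which is a reason to name the treatment contrast in advance rather than correct over all pairs.

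**The case against.** The strongest defence is that one time structure serves all outcomes. Baseline is the only occasion before therapy that every primary and secondary scale shares, so a common baseline is a defensible choice. The article also does not say that pretreatment data will be excluded, and a fuller plan may use them in a sensitivity analysis. This stands as a reason not to call the values discarded. It does not remove the point: the article lists the time levels of its main model, the list starts before therapy, and for distress and gaming time a value closer to the start of treatment is scheduled.

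Several stronger readings are tempting, and the document does not support them:

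- **That the effect is biased upward.** The length of the interval and the direction of change in it are not given. If patients worsen while waiting, the bias reverses. Improvement is the likelier direction in people seeking treatment, but that is a judgement.
- **That the interval is an untreated control period.** The protocol does not call it untreated. It is an uncontrolled run-in and can address natural course only in part.
- **That the protocol names regression to the mean as its main limitation.** It names the single-arm design, and among rival explanations the natural course. Regression to the mean is not mentioned.
- **That a false finding is about as likely as not.** A figure near 51% arises for a 0.3 SD drift at rho = 0.7 if the test is run at an unadjusted 0.05. The plan specifies Bonferroni, which gives 33% on those inputs and 19% at rho = 0.5.

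**Conclusion.** The point holds for CORE-OM, RCADS-child, RCADS-parent and time spent gaming. As written, the model counts any change before therapy as treatment-phase change, and the scheduled value that would separate the two has no stated role. For GDT, IGDS9-SF, GAIT-parent and the secondary scales the same change may be included, but the scheduled data cannot separate it, so only a stated limitation is available.

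The size cannot be read from the document. Over drifts of 0.1 to 0.3 SD and correlations of 0.5 to 0.7, the corrected baseline-to-post comparison for gaming time would be significant 3% to 33% of the time with no change after therapy starts. This range rests on assumed drift, assumed correlation, equal variances and n = 28. It illustrates how sensitive the comparison is and does not predict this trial's result. The change is worth making because it needs no new data and bears on a weakness that the protocol acknowledges.

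**What to change.** In Statistical Analysis and Power Analysis:

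1. For CORE-OM, RCADS-child, RCADS-parent and time spent gaming, fit time with four levels: baseline, pretreatment, posttreatment and follow-up.
2. Name pretreatment-to-posttreatment as the treatment contrast for these outcomes.
3. Report baseline-to-pretreatment change beside it with its 95% CI, described as a partial check on natural course and not as a control comparison. A comparison of change per week between the two intervals should not be promised, because the article gives no interval lengths.
4. State that GDT, IGDS9-SF, GAIT-parent and the secondary scales have no pretreatment value, so their change from baseline includes any change during the assessment period.

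The cost is wording: the values are already scheduled and the overall test needs no more patients on the assumptions above. There are two downsides. The estimated effect on distress and gaming time may be smaller, and the reference point will differ between outcomes, which the report must make clear.
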